| This study commenced in Melbourne (Alfred Hospital) in October 2000, and by the end of 2001 we are on schedule to have recruited 20 participants. We are aiming to study approx. 36 individuals in total to give what we believe will be adequate power to detect differences between treatment groups in airway inflammatory markers. We are looking to recruit a further 16 COPD sufferers in Hobart over the first half of 2002. |                             |                      |
| Thus the specific aim of this application is to allow completion of a study that [name] started in Victoria, and now wishes to transfer to Tasmania. From a scientific and clinical perspective the study will give significant insights into the patho-physiology of COPD and the effects of ICS on the patients.                                                                                                            |                             |                      |

|                                                                                                                                                                                                                                                                                                                                                      |          |                 |                                                |
|------------------------------------------------------------------------------------------------------------------------------------------------------------------------------------------------------------------------------------------------------------------------------------------------------------------------------------------------------|----------|-----------------|------------------------------------------------|
| Period of investigation vi                                                                                                                                                                                                                                                                                                         |          |                 |                                                |

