## B. PROCEDURES

### Detailed proceduresix

#### Outline of Protocol:

- This will be a double-blind, placebo controlled, parallel group study.
- Subjects will be randomised 2:1 to receive active medication (Fluticasone 500 mcg bd) or placebo bd, both given in the same way via identical dry powder, "Diskus" devices for a duration of 6 months.
- After recruitment, but before initiation of randomised therapy, each patient will undergo:
  - Full spirometry with a flow-volume loop, before and after 200 mcg inhaled salbutamol (a  $\beta$  agonist bronchodilator) given via a spacer device.
  - A Quality Of Life Questionnaire (QOL) (St George's Respiratory Questionnaire) will be completed.
  - Induction of sputum (by spontaneous coughing or by our standard laboratory method of nebulisation of hypertonic saline, if necessary).
- At least 48 hours later, standard flexible fiberoptic bronchoscopy will be performed under local anaesthetic, with 6 endobronchial biopsies being taken from around the orifices of middle or lower lobe bronchi, and a standard 3 X 60 ml bronchoalveolar lavage (BAL) will be performed. Before bronchoscopy, 200 mcg of salbutamol and 80 mcg of ipratropium bromide will be given by inhaler. Supplemental oxygen will be given throughout the procedure and oxygen saturation will be monitored using a finger probe from a pulse oximeter.
- At the end of the study period, these four procedures will be repeated ie questionnaire, pulmonary function, sputum collection and bronchoscopy (with the latter at least 48 hours later to avoid any confounding by potential acute cellular changes induced by sputum induction). Study medication will continue until these investigations are complete.

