#### Study outcome measures/efficacy measurements

- Changes in the QOL measure and spirometric values (large and small airway flow rates)
- Sputum neutrophil and eosinophil percentage counts
- Bronchoalveolar lavage cell differential counts and FACS analysis (lymphocyte and macrophage subtypes and activation markers). BAL supernatant will be stored for cytokine and chemokine assays and assay of selected mediators, eg ECP, neutrophil elastase and myeloperoxidase.
- Airway biopsies: the initial emphasis will be on acute and chronic cellular inflammation: numbers of eosinophils, neutrophils, lymphocytes and macrophages and activation markers HLADR and CD25 but with the potential for later study of indices of scarring and "remodelling" of the airway wall ie collagen I, III and V deposition, epithelial integrity, subepithelial basement membrane thickness and degree of vascularity in the subepithelial lamina propria area (by collagen IV staining).

**NB** Over the past 15 years of research into airway pathology using fibre-optic bronchoscopy, we have developed a wide range of end points with which to assess both BAL and biopsy material. The degree to which we can fully utilise the material will depend upon funding over the next three years. However, we already have sufficient funding to allow assessment of acute and chronic cellular infiltrates in the airway, which is our primary pathological endpoint. Further grant applications will be developed over the next 12-18 months, based upon this study protocol, the extremely valuable biological material obtained and our extensive "track record" in this field of research (see references).

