#### Statistical Analysis

At the end of the study we will intend to have 24 paired sets of data in volunteers treated with active intervention (Fluticasone) and 12 in placebo treated controls.

There will be 4 main approaches to analysis:

- Baseline bronchoscopic data as a whole will be analysed against our current historic normal control data, of which we have large numbers both for airway biopsy (n=24) and BAL (n=36). This will give us excellent power to detect even subtle changes within COPD cell profiles (and later structural components).
- The placebo control material will be used to establish stability over time in biological signals and to establish coefficients of repeatability for cellular indices. Paired analysis within the actively treated group will be undertaken to indicate which cellular populations or activation markers may be susceptible to change with ICS, and then changes over time in these indices will be compared with respective changes in the placebo treated control material. We have previously published repeatability data in chronic stable asthmatics, and done similar calculations in post lung transplant airway samples, which indicate that optimal power for detecting changes with time is achieved with approx. 15 data pairs for most cell lines. With the numbers available in this COPD study, we therefore have substantial "reserve".
- The central analysis will focus on the ICS treated group and use changes over time in both cellular indices (in BAL and biopsies) and clinical and physiological end points, and undertake regression analyses to define which, if any, of the cellular changes are related to clinical and/or physiological improvements.

- We will perform post-hoc analyses in selected sub-groups, namely:
  - a) those in whom regular sputum production is a feature.
  - b) those with above normal airway eosinophils.
  - c) those with more or less severe lung function abnormalities (best and worse 10) to define whether ICS have more benefit in these patients than in COPD in general.

This will be a large and complex data set, but we have extensive experience in relating clinical, physiological and bronchoscopic pathological end points. We have developed close collaboration with [name] and [name], our statistical advisers at Monash University, and they will again by providing assistance with this study.

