## SUBJECTS

### Selection of subjects x

#### Inclusion criteria:

- Age 40-70 years
- 36 subjects with smoking-related COPD to complete the study, which will mean likely need for initial recruitment of up to 45 patients (both male and female will be included).
- Minimum of 15 pack-year history of cigarette smoking. Either current or ex smokers.
- FEV1 40% to 80% predicted and/or FEF50<50% with FER (ratio of FEV1 to FVC)  $\leq 70\%$  post bronchodilator and definite scalloping out of the descending limb of the flow-volume loop on spirometry. Absolute FEV  $\geq 1.5$  litres.
- Bronchodilator therapy with a short acting beta agonist prn and anticholinergics in stable doses will be allowable.

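### SGRQ and spirometry are listed as efficacy measures in a placebo-controlled trial, but the only fluticasone-versus-placebo comparison the protocol states is for cellular indices

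*Protocol*

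**What the plan says.** The Outline of Protocol sets the design: "This will be a double-blind, placebo controlled, parallel group study", and "Subjects will be randomised 2:1 to receive active medication" or placebo for 6 months. SGRQ and spirometry are measured in every subject before treatment (Visit 2) and at 6 months (Visit 6).

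The list of outcome and efficacy measures opens with "Changes in the QOL measure and spirometric values (large and small airway flow rates". Sputum, lavage and biopsy measures follow.

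The Statistical Analysis section expects "24 paired sets of data in volunteers treated with active intervention (Fluticasone) and 12 in placebo treated controls" and names four main approaches:

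1. Baseline bronchoscopic data against historic normal controls.
2. Repeatability in the placebo arm, then a paired analysis of cell populations and activation markers in the active arm, after which "changes over time in these indices will be compared with respective changes in the placebo treated control material".
3. A central analysis concentrating on the fluticasone arm, using regression to "define which, if any, of the cellular changes are related to clinical and/or physiological improvements".
4. Post-hoc subgroups, asking whether the steroid gives more benefit there than in COPD generally.

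The Justification field states the aim of the sample size as "adequate power to detect differences between treatment groups in airway inflammatory markers".

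**The concern.** Randomisation and a placebo arm allow a change seen on treatment to be set against the change that would have happened anyway. The plan uses this for the cells and does not say that it will for SGRQ or spirometry. Its third and fourth approaches nevertheless speak of clinical improvement and of benefit from the steroid, and the stated hypothesis concerns that benefit.

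With no stated placebo contrast, improvement can only mean change over 6 months in patients who took fluticasone. Placebo response, season and the extra attention of a trial all contribute to that change. Likewise, an association between cellular and clinical change found only among treated patients cannot be attributed to the steroid, because the same association might exist among placebo patients. The placebo data that would settle both questions are collected but are given no stated role for the clinical end points.

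**Working it through.** **Step 1. The plan's own numbers.** The Inclusion criteria ask for "36 subjects with smoking-related COPD to complete the study, which will mean likely need for initial recruitment of up to 45 patients". At 2:1, 36 × 2/3 = 24 and 36 × 1/3 = 12, as stated. Recruiting 45 implies a loss of 1 − 36/45 = 20%, and 36/0.80 = 45. These figures agree.

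**Step 2. Look for a between-arm contrast in each approach.**

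| Approach | Data | Comparison stated | Fluticasone v placebo on SGRQ or spirometry? |
|---|---|---|---|
| 1 | Baseline bronchoscopy | COPD v historic normals | No |
| 2 | Cell populations, activation markers | Within active arm, then v placebo | No, cellular only |
| 3 | Cellular, clinical and physiological change | Regression, focused on the active arm | No |
| 4 | Post-hoc subgroups | Subgroup v COPD generally | None named |

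In approach 2 the phrase about indices refers back to cell populations and activation markers. The same paragraph gives the placebo material a role in the repeatability of cellular indices, which fits that reading. The sample-size statement in the Justification field also speaks of treatment-group differences in inflammatory markers only.

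**Step 3. What a shared change does to the regression in approach 3.** Suppose that within the active arm clinical change = a + b × cellular change + error. Adding a constant s to every patient's clinical change gives (a + s) + b × cellular change + error. The intercept moves and the slope b does not. A constant shared shift therefore does not create or distort the association. What remains is that b, estimated in one arm, cannot be attributed to the drug, and that the average improvement, which contains s, has no placebo anchor.

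**Step 4. Size, if a before-after clinical claim were made.** The protocol gives no placebo change, SD, significance level or power for the clinical end points. Assumptions: two-sided 5%, unit = SD of the 6-month change, zero drug effect, and a range of shared changes. The one-sample t-test with n = 24 has non-centrality d√24.

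| Shared change d | Before-after test, n = 24, significant | 24 v 12 test, significant |
|---|---|---|
| 0.2 SD | 15.6% | 5.0% |
| 0.3 SD | 29.1% | 4.9% |
| 0.5 SD | 65.0% | 4.9% |

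The first column of percentages is from the non-central t distribution; the second is from 100,000 simulated trials.

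**Step 5. Precision of the between-arm comparison.** The standard error of the difference in mean change is SD × √(1/24 + 1/12) = 0.354 SD. The 95% CI half-width is 2.032 × 0.354 = 0.72 SD (34 degrees of freedom). For the before-after mean in 24 patients it is 2.069 × √(1/24) = 2.069 × 0.204 = 0.42 SD.

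The difference detectable with 80% power is:

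- between arms, (1.960 + 0.842) × 0.354 = 0.99 SD by the normal approximation, 1.02 SD by the t-test;
- before-after, (1.960 + 0.842) × 0.204 = 0.57 SD by the normal approximation, 0.60 SD by the t-test.

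A true effect of 0.60 SD has 80% power in the before-after test and about 38% between arms.

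**The case against.** **The study is mainly mechanistic.** The aim is to describe the infiltrate and relate it to response; the sample size is argued on inflammatory markers; and for those markers the arms are compared. The outcome list is not ranked, so being listed first does not make SGRQ or spirometry primary. This stands, and it limits the seriousness of the point. It does not explain why measures listed under efficacy should lack a stated comparison with placebo.

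**A statistical analysis plan may add the comparison.** The four approaches are called the main ones, statistical advisers are named, and nothing forbids a clinical contrast. This also stands: the supportable claim is that no comparison is stated, not that none will be made. But which outcomes are compared between randomised arms is something the protocol itself addresses. It specifies that contrast for cells and places the clinical end points in an analysis of one arm. An analysis plan that followed this would inherit the gap.

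**The false-positive rates describe a test the protocol does not plan.** This is correct. The paired analysis in the active arm is of cellular measures, and clinical end points enter only a regression. The rates show the risk of a before-after clinical claim; they are not the error rate of any stated analysis.

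**Regression to the mean and practice effects are limited.** Eligibility is judged at Visit 1, and baseline spirometry is repeated at Visit 2 after at least a week of run-in and a stability check. Much of the regression to the mean from entry selection, and some practice effect, therefore falls before baseline. Placebo response, season and trial care are not removed this way.

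**Conclusion.** The point holds in a limited form. The protocol states a fluticasone-versus-placebo comparison for cellular indices only, and uses SGRQ and spirometry only in an analysis focused on the treated arm. Any clinical improvement or benefit reported under that plan would be change from baseline, without a placebo anchor, although the placebo data exist. It should be corrected, but it does not undermine the trial or its cellular comparison.

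A reader might infer three stronger things, and the document supports none of them. First, that the arms will never be compared clinically: the protocol does not say so. Second, that the planned analysis has a false-positive rate of up to 65%: that figure needs an assumed shared change of 0.5 SD and a before-after clinical test that is not stated. Third, that a shared change would produce spurious links between cells and improvement: a constant shift leaves the slope unchanged. Only variation between patients that is related to cellular change could do that, and its size cannot be judged from the document.

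All figures in SD units rest on an assumed two-sided 5% level, and the detectable differences also on 80% power. The allocation of 24 and 12 is the protocol's own.

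**What to change.** In the Statistical Analysis section, extend the between-arm comparison to SGRQ total score and the spirometric measures. For each, regress the Visit 6 value on treatment arm and the Visit 2 value, and report the fluticasone-minus-placebo difference with a 95% CI. Base any statement that the steroid gives clinical or physiological benefit on that difference. Describe changes within the fluticasone arm as change from baseline.

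The cost is about a sentence of protocol text and one regression per clinical end point. It needs no new patients, visits or measurements. The drawback is lower precision than the before-after figure: without baseline adjustment, a half-width of about 0.72 SD instead of 0.42 SD. Adjustment may narrow the between-arm interval somewhat, depending on a baseline-to-follow-up correlation that the protocol does not give. Clinical claims will be more modest, and the text should say that 24 versus 12 can reliably detect only differences of about 1 SD.

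### The ICS-versus-placebo comparison of cellular indices is written as change against change with no baseline term; adjusting for baseline would usually be more precise at 24 versus 12, at almost no cost

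*Protocol*

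**What the plan says.** The second of the four approaches under Statistical Analysis first makes a paired analysis within the fluticasone group. It then says that "changes over time in these indices will be compared with respective changes in the placebo treated control material". The indices meant are cell populations and activation markers. No baseline covariate, model, test or transformation is named. This is the only comparison with the randomised placebo arm that the section spells out.

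The planned size is given in the same section: "we will intend to have 24 paired sets of data in volunteers treated with active intervention (Fluticasone) and 12 in placebo treated controls". That agrees with the allocation in the Outline of Protocol ("Subjects will be randomised 2:1 to receive active medication (Fluticasone 500 mcg bd) or placebo bd"). The Justification section rests the sample size on a comparison of arms: "We are aiming to study approx. 36 individuals in total to give what we believe will be adequate power to detect differences between treatment groups". The Outline of Protocol has the questionnaire, spirometry, sputum and bronchoscopy done before treatment and repeated at the end, so every completer should have a baseline value.

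The outcome list also includes "Changes in the QOL measure and spirometric values (large and small airway flow rates"), but Statistical Analysis states no between-arm method for these measures.

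**The concern.** A change score subtracts the whole baseline value. When baseline and 6-month values correlate at less than 1, that is more correction than the data support, and noise in the baseline is carried into the result. Noisy measures suffer most. The protocol itself treats the repeatability of its cell counts as something still to be established from the placebo arm.

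With only 24 and 12 patients, the arms can differ appreciably at baseline by chance. An arm that starts high tends to fall back, and an unadjusted change score counts that fall as part of the treatment difference. At stake is the precision of the one controlled comparison set out, in a trial too small to give precision away.

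**Working it through.** **The plan's own figures.** 24 + 12 = 36, as stated, in a 2:1 ratio. Recruiting up to 45 for 36 completers implies a loss of 1 − 36/45 = 20%. The power statement cannot be reproduced: no alpha, power, effect size, SD or correlation is given. The other statement on power, that "optimal power for detecting changes with time is achieved with approx. 15 data pairs for most cell lines", concerns paired data within a group and also gives no inputs.

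**Inputs.** From the protocol: 24 and 12 completers. Assumed: r = 0.3 to 0.7 between baseline and 6 months (wider values shown), equal SD at both visits, the same baseline slope in both arms, two-sided alpha 0.05. All results are in units of the SD of a single measurement.

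**Variance of the treatment difference.** Let k = 1/24 + 1/12 = 0.125.

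- Change score: 2(1 − r)k.
- Adjusted for baseline, large samples: (1 − r²)k. The reduction is (1 − r)/2, that is 35%, 25% and 15% at r = 0.3, 0.5 and 0.7.
- Adjusted, with the slope estimated from 36 patients: multiply by (36 − 3)/(36 − 4) = 33/32 = 1.031.

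| r | Change score | Adjusted, large sample | Adjusted, with 33/32 | Net reduction | Simulated |
|---|---|---|---|---|---|
| 0.3 | 0.1750 | 0.1138 | 0.1173 | 33.0% | 32.9% |
| 0.5 | 0.1250 | 0.0938 | 0.0967 | 22.7% | 22.3% |
| 0.7 | 0.0750 | 0.0638 | 0.0657 | 12.3% | 12.3% |
| 0.9 | 0.0250 | 0.0238 | 0.0245 | 2.0% | 2.2% |
| 0.95 | 0.0125 | 0.0122 | 0.0126 | −0.5% | −0.4% |

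The simulation used 40,000 trials of 24 versus 12 at each r.

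**Power.** These figures use the noncentral t distribution, with 34 degrees of freedom for change and 33 for the adjusted analysis. The difference detectable with 80% power, change score against adjusted, is 1.21 against 0.99 SD at r = 0.3, 1.02 against 0.90 at r = 0.5, and 0.79 against 0.74 at r = 0.7. Where the change-score test has 80% power, the adjusted test has 92.8%, 88.9% and 84.8% respectively, and 80.7% at r = 0.9.

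**Baseline imbalance.** The baseline difference between arms has SD √0.125 = 0.354, so it exceeds 0.5 SD in about 16% of trials for any one index. Given a baseline difference d, the change-score difference shifts by −(1 − r)d. At r = 0.5 and d = 0.5 SD the shift is 0.25 SD. This is the precision loss seen from another side: 2(1 − r) = (1 − r²) + (1 − r)², which at r = 0.5 is 1.00 = 0.75 + 0.25, and the 0.25 is the contribution of chance imbalance.

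**Sensitivity to equal variances (large sample, r = 0.3 to 0.7).** If the 6-month SD is 0.7 times the baseline SD, the reduction is 58% to 51%. If it is 1.3 times, the reduction is 19.5% to 0.9%.

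**The case against.** The strongest reply is that nothing here is wrong. A comparison of change scores is unbiased over randomisation, and the sentence does not exclude adjustment: analysis of covariance of the change, with baseline as covariate, gives the same treatment estimate as analysis of the 6-month value. Covariates and transformations are often left to a statistical analysis plan, and none is shown. This stands as far as it goes. A reader might infer that the protocol prescribes an expressly unadjusted analysis, or an invalid one; the documents support neither. What remains is that the protocol names change against change as the comparison and does not ask for the baseline term.

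A reader might also take a gain of 15% to 35% as established. Those are large-sample values for an assumed r and equal variances. The net figures at this size are lower, and for an index that tracks closely over 6 months the gain disappears. Nor is adjustment strictly free, since it uses a degree of freedom and pays for estimating the slope.

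Two limits on scope also stand. The quoted sentence covers cellular indices only; listing changes in quality of life and spirometry as outcomes does not show how the arms will be compared on them. And the analysis that the protocol calls central is a regression within the ICS group, which this point does not reach.

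Finally, a plain log scale would fail on zero eosinophil counts. The common-slope assumption may also be strained for eosinophils, because the stated hypothesis is that benefit is greatest where airway eosinophilia is most marked.

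**Conclusion.** The point holds as a recommendation for efficiency. The size of the gain rests on assumed values of r, on equal variance at both visits and on a common slope; the protocol supplies none of these. Over the assumed range the gain is material for a trial of 36, and at r = 0.5 it is equivalent to about 36/(1 − 0.227) ≈ 47 patients analysed by change score. Where r is very high, the possible loss is negligible. Precision and the pull of baseline imbalance should be counted as one effect; reading them as two separate harms would double the case.

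**What to change.** State in Statistical Analysis that the between-arm comparison of each cellular index will use analysis of covariance of the 6-month value (or, equivalently, of the change) on treatment and the baseline value of the same measure. The scale should be a suitable transformation that handles zero counts. Show the changes descriptively. Use the same model for any between-arm comparison of the St George's questionnaire and spirometry.

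The cost is a sentence or two of text, one degree of freedom (34 to 33) and about 3% in variance. No extra patients, visits or measurements are needed. The regression within the ICS group is unaffected.

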| Research                                                                                                                                                                                                                                                                                                                                                                                                                            |                             |                      |
| Aims iv                                                                                                                                                                                                                                                                                                                                                                                                           |                             |                      |
| To describe the range of airway inflammatory infiltrate in a group of patients with mild to moderate COPD, and to relate that cell picture to the response to ICS therapy over a 6 month period.                                                                                                                                                                                                                                    |                             |                      |
| The Hypothesis is that positive benefit of ICS therapy in COPD patients is most marked in those with the most prominent degree of airway eosinophilia.                                                                                                                                                                                                                                                                              |                             |                      |
| Justification v                                                                                                                                                                                                                                                                                                                                                                                                   |                             |                      |

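### The analysis called central regresses change on change with a focus on the ICS arm, so the stated hypothesis of greater ICS benefit with more airway eosinophilia gets no planned placebo-controlled test.

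*Protocol*

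**What the plan says.** The Aims section of the Protocol states one hypothesis: "positive benefit of ICS therapy in COPD patients is most marked in those with the most prominent degree of airway eosinophilia". The aim above it is to describe the airway infiltrate and "to relate that cell picture to the response to ICS therapy over a 6 month period". The Outline of Protocol sets the design: "This will be a double-blind, placebo controlled, parallel group study", with 2:1 allocation to fluticasone or placebo.

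The Statistical Analysis section plans for "24 paired sets of data in volunteers treated with active intervention (Fluticasone) and 12 in placebo treated controls" and lists four approaches:

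1. Baseline bronchoscopic data are compared with historic normal controls.
2. Placebo data establish stability and repeatability of cellular indices. Changes in those indices on active treatment are then compared with the changes on placebo.
3. "The central analysis will focus on the ICS treated group and use changes over time in both cellular indices" and in clinical and physiological end points, and will "undertake regression analyses to define which, if any, of the cellular changes are related to clinical and/or physiological improvements".
4. Subgroup analyses, labelled post hoc, include (b) patients with above-normal airway eosinophils. The stated question is whether ICS helps these patients more than it helps COPD patients in general.

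**The concern.** The hypothesis concerns effect modification: does the difference between fluticasone and placebo grow with the patient's eosinophil level? The central analysis departs from it in three respects.

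- **Population.** It concentrates on the ICS arm. A within-arm slope combines any drug-specific relation with whatever links cells and outcomes regardless of treatment, such as exacerbations, natural fluctuation and regression to the mean.
- **Predictor.** It uses the change in cells over six months, which is measured after randomisation. The hypothesis is about the degree of eosinophilia a patient has.
- **Target.** It searches across cell indices and end points for any that are related. Eosinophils are not singled out.

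A positive slope could be taken as support for the eosinophil hypothesis when the same slope exists on placebo. The randomised control guards against that error, but the plan assigns it no part in this analysis.

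**Working it through.** **1. Planned numbers.** 36 completers split 2:1 give 24 and 12, as stated. Recruiting up to 45 implies a loss of 1 − 36/45 = 20%. No alpha, power, effect size or SD is stated, so there is no power figure to reproduce. Everything below assumes a two-sided 5% level and normal data.

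**2. Each approach against the hypothesis.** A test needs clinical or physiological benefit, eosinophil level and the placebo comparison together.

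| Approach | Clinical benefit | Eosinophil level | Placebo comparison |
|---|---|---|---|
| 1. Baseline vs normals | no | yes, at baseline | no |
| 2. Repeatability and cellular change | no | only as change in cells | yes |
| 3. Central regression | yes | only as change in cells | none stated |
| 4(b). Subgroup, post hoc | yes | yes, above normal | none stated |

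No row has all three.

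**3. What an ICS-only slope can show.** Simulated trials of 24 versus 12, with the same cell-outcome correlation in both arms and so no drug-specific relation. The correlations are assumptions; the Protocol gives none.

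| Correlation in both arms | ICS-only regression significant | Arm × marker interaction significant |
|---|---|---|
| 0.2 | 16% | 5% |
| 0.3 | 30% | 5% |
| 0.4 | 51% | 5% |
| 0.5 | 73% | 5% |

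Both tests here use the same marker, so the table isolates the effect of leaving out placebo. It does not compare baseline eosinophils with change in cells as a predictor.

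**4. Multiplicity.** The Study outcome measures section lists many cell indices and several outcomes without a count. Assume 10 indices and 3 outcomes, hence 30 regressions, with no true relation. If they are independent, the chance of at least one p < 0.05 is 1 − 0.95^30 = 79%. Simulation with n = 24 gives about 60% when indices correlate at 0.5 with each other and outcomes likewise, and about 45% at 0.7 and 0.6. These correlations are also assumptions.

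**5. Precision of a both-arm interaction test.** In residual SD per SD of eosinophils, the standard error of the slope difference is about √(1/23 + 1/11) = 0.367. The normal approximation for 80% power is then 2.80 × 0.367 = 1.03. That is optimistic at this size. Simulation with the t test gives:

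| Slope difference | Power |
|---|---|
| 0.5 | 25% |
| 0.75 | 48% |
| 1.0 | 70% |
| 1.15 | 81% |

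**The case against.** Placebo is not discarded. The second approach compares cellular change between arms, and the Justification section ties the 36 subjects to differences between treatment groups in inflammatory markers. The drug-to-cell step is therefore controlled. This stands, and it rules out the inference that the plan ignores its placebo arm. What lacks control is the link from cells to clinical benefit.

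Baseline eosinophils are not confined to the subgroup, because the first approach analyses all baseline bronchoscopic data. That is also correct. The supportable claim is narrower: no other listed analysis relates eosinophil level to ICS benefit.

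The subgroup is named in advance, so its post-hoc label is partly a misnomer, and the text does not restrict it to ICS patients. Both points stand. It still states no comparison with placebo patients at the same eosinophil level.

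A reader might take the 16% to 73% as false-positive rates of the planned regression. They are not. The simulated correlation is real, and the regression asks only whether cell changes and improvements are related. The error arises if the result is read as specific to ICS or as support for the eosinophil hypothesis, and the Protocol does not say it will be read that way. Nor is 79% the plan's error rate: it needs 30 independent tests, which the Protocol does not state.

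Finally, a separate statistical analysis plan may exist. It could supply model detail, but this Protocol already fixes what is central, in which patients and with which variables.

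**Conclusion.** The point holds as a structural mismatch: as written, the plan gives its only stated hypothesis no pre-specified, placebo-controlled test. This follows from the text and does not depend on the simulations.

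The figures show the possible scale under stated assumptions. An ICS-only slope would be significant in about 16% to 73% of trials if a correlation of 0.2 to 0.5 exists in both arms. The search would add roughly a 45% to 79% chance of at least one false positive if there are 30 tests.

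It would go too far to infer that the trial cannot address the hypothesis. The design and the scheduled measurements allow a controlled test, but one able to confirm only a large effect modification. The mismatch should be corrected before analysis because it concerns the analysis the Protocol itself ranks first.

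**What to change.** Make the eosinophil question the central analysis, as one model in all randomised patients with paired data:

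6-month response = baseline response + arm + baseline airway eosinophils (continuous) + arm × baseline eosinophils

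Name one response measure in advance, either a single spirometric value or the St George's total score. Test the interaction and report it with its confidence interval. Keep the ICS-only change-on-change regressions and the eosinophil subgroup as exploratory, and say that a slope within the ICS arm is not evidence of an ICS-specific relation. The scale for eosinophils and any further covariates can be left to the statistical analysis plan.

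The cost is protocol wording and one model on data already scheduled. The price in precision is substantial and should be stated: power is about 25% for a slope difference of 0.5 residual SD per eosinophil SD and about 70% for 1.0, with 80% reached only near 1.15. A non-significant interaction must therefore not be reported as absence of effect modification.
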